**Problem statement:** Poor adherence is a major threat to successful ART outcome in Malaysia (Malaysia NSP, 2011-2015) and generates major concerns about growing resistance of HIV to the currently available ARVs (WHO, 2007). Poor adherence leads to treatment failure, disease progression and death (WHO, 2007). With treatment failure, the preventive opportunity that ARVs provide is also lost (WHO, 2007). Poor adherence has grave socioeconomic impact on program funding – second line medications are more expensive and complex (WHO, 2007). Effectiveness of routine adherence counseling on treatment adherence among ART patients has not been previously studied in Malaysia. Similarly, factors affecting adherence to ART has not been extensively studied in Malaysia.

**Significance of research:** This research is in line with Key activity 6 of Strategy 2 in the current drive by Malaysian Government to improve adherence to treatment and detection of treatment failure (Malaysia NSP, 2011-2015). It is also consistent with current WHO recommendation of interventions to optimize adherence to ART (WHO, 2013). It will contribute to existing body of knowledge on factors associated with treatment default and LTFU among HIV patients on ART. Its results will provide baseline information on effectiveness of current standard of care (routine adherence counseling) on treatment adherence and clinical outcomes. It will provide an opportunity to test the effectiveness of the intervention as a tool/strategy to improve patient retention. The outcome will provide information to Government for policy decisions in improving service delivery for HIV patients, reduce cost of HIV treatment programs and scale-up to other locations across Malaysia.

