### Research hypotheses:

**H1:** There is no significant difference in the socio-demographic characteristics of HIV patients who adhere very well to their ART compared to those who do not.

**H2:** The application of mobile phone technology (SMS and phone call reminders) will significantly improve treatment adherence and clinical outcomes of HIV patients on ART, when compared to routine adherence counselling and paper-based appointment scheduling alone.

**H3:** There is a strong and direct relationship between Good adherence to treatment (regular clinic visits and strict medication adherence) and outcome of antiretroviral treatment among HIV patients on ART.

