| Clinical (Wt, TB & OI status)                   | Clinician's notes       | Clinicians/nurses/adherence counsellors          | Every visit                                       |
| Immunological (CD4)
Virological (viral load) | Laboratory records      | Laboratory scientists                            | Baseline & 6mths                                  |
| Medication adherence                            | Adherence questionnaire | Research assistants/nurses/adherence counsellors | Baseline, then every visit (particularly 3&6mths) |

- **Data Storage:** All data generated from this study will be stored for a maximum of 3 years after the completion of the study, after which they will be destroyed. However, during this period they will remain joint intellectual property of Universiti Putra Malaysia and Hospital Sungai Buloh.

**Primary Outcomes:** The first primary outcome is (improved) patient adherence to ART at six months. This is assessed by self-report using a standardized questionnaire of the number of pills missed in the last 30 days and calculating percent adherence based on the expected number of doses taken and/or number of missed doses. Percent adherence will be analyzed as continuous variable and polytomous variable. Subjects will be considered as "Good adherence" when they achieve an optimal adherence cut of >95% of medications taken as directed with <3 missed doses in the last 30 days period. "Fair adherence" will be considered as 80-95% of medications taken as directed with 3-8 missed doses in the last 30 days period, while "Poor adherence" will be considered as <80% of medications taken as directed with >8 missed doses in the last 30 days period. Medication adherence will be assessed at each follow-up visit, particularly at months 3 and 6. The six month scheduled follow-up is the primary analysis but the three month assessment will allow for evaluating trends but is not the primary outcome.

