The second primary outcome is (regularity of) scheduled clinic attendance at six months. This will be assessed from records of scheduled clinic visits in the medical records unit and supported by record of scheduled drug pick-up in the pharmacy. Regularity of scheduled clinic visits will be calculated based on number of scheduled clinic visits attended and/or number of times defaulted. Number of missed appointments will be analyzed as a continuous variable and polytomous variable. Subjects will be considered as "Regular clinic attendee" if they never missed any scheduled clinic appointment. A "Defaulter" will be a patient who has missed one or more scheduled clinic appointment for any reason(s), while a patient will be considered "Lost-to-follow-up" if s/he refuses to show up for scheduled clinic visit for 3 consecutive months, after 3 consecutive attempts to track the client and bring them back on treatment. The six month scheduled follow-up is the primary analysis but the three month assessment will allow for evaluating trends.

**Secondary Outcomes:** The first secondary outcome is (improved) clinical status of patients at six months. This will be assessed by measuring their weights, assessing their TB and opportunistic infection status at every clinic visits, particularly at three and six months and comparing these with the baseline status. Patients' weight is routinely measured and recorded by nurses at the study site, as part of standard patient management protocol. These records will be accessed and utilized in the analysis. Patients' TB status is also routinely assessed and recorded by clinicians/nurses/adherence counselors at every clinic visits. These records will be accessed and utilized to categorize patients into four groups, namely "No signs and symptoms of TB", "TB suspected and referred for evaluation", "Currently on INH prophylaxis" and "Currently on TB treatment". Opportunistic infection status will be assessed through WHO clinical staging at every clinic visits. The six month scheduled follow-up is the primary analysis but trend will be evaluated at three months.

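### Month-6 clinical status is defined only for patients who attend, and death is in no outcome except, implicitly, as a missed appointment

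*Protocol*

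**What the plan says.** Under Secondary Outcomes, the protocol defines clinical status at six months by three findings: "This will be assessed by measuring their weights, assessing their TB and opportunistic infection status at every clinic visits". On TB: "Patients' TB status is also routinely assessed and recorded by clinicians/nurses/adherence counselors at every clinic visits". These records sort patients into four groups, none of them for a patient who died or was not seen. On opportunistic infection: "Opportunistic infection status will be assessed through WHO clinical staging at every clinic visits". On timing: "The six month scheduled follow-up is the primary analysis but trend will be evaluated at three months". The table under Data collection names the clinician's notes, at every visit, as the source of these clinical data, and lists no item for vital status.

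Death is not part of any primary or secondary outcome. Yet the Problem statement says "Poor adherence leads to treatment failure, disease progression and death", and under Sampling unit patients with WHO stage 3 and 4 disease are eligible.

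Under Primary Outcomes, a Defaulter is a patient who "has missed one or more scheduled clinic appointment for any reason(s". Loss to follow-up requires that the patient refuses to come for three consecutive months, after three tracking attempts.

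H2 states that the reminders "will significantly improve treatment adherence and clinical outcomes of HIV patients on ART". Expected outcomes anticipates a difference between arms in both clinic attendance and clinical outcome. Data analysis names intention-to-treat and complete case analysis.

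**The concern.** Two things follow from these definitions. First, the gravest harm that the protocol attributes to poor adherence never counts as a clinical failure. On a literal reading it enters only as default, so the attendance outcome mixes patients who died with patients who stayed away.

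Second, being observed at month 6 depends on attendance, which the intervention is designed to change. Patients with a month-6 clinical status are then not comparable between arms, even though the randomised groups were. If ill patients attend less, or more patients die in the control arm, the control patients who are seen look healthier than the control group as a whole. At stake is the clinical part of H2: a real benefit could be diluted or lost.

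**Working it through.** There is no figure in the plan to reproduce. The protocol gives no mortality, clinical event or attendance rate by arm, and its sample size (121 per group) rests on CD4 count. The check is first of the text, then an illustration with assumed rates.

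**1. A patient who dies before the month-6 visit, traced through each outcome**
- Adherence: self-report at six months, so no answer.
- Attendance: an appointment is missed, so the patient is a Defaulter. Loss to follow-up does not fit, because it requires refusal.
- Clinical status: no weight, TB group or stage at month 6.
- Immunologic status: no month-6 CD4 count or viral load.

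Only the Defaulter category registers the event.

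**2. Dilution among attenders**
Assumed: event risk 10% in attenders and 30% in non-attenders in both arms; month-6 attendance 95% (reminder) and 85% (control).
- True risk, reminder: 0.95 × 0.10 + 0.05 × 0.30 = 0.110 (13.3 per 121).
- True risk, control: 0.85 × 0.10 + 0.15 × 0.30 = 0.130 (15.7 per 121).
- Among attenders: 0.095/0.95 = 10.0% against 0.085/0.85 = 10.0%.

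A true 2-point benefit disappears.

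**3. Attendance that depends on illness, and deaths**
Let b be the true proportion with bad status including deaths, d the proportion dead, and a_ill and a_well the month-6 attendance of living ill patients and of well patients. Then

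observed = (b − d) × a_ill / [(b − d) × a_ill + (1 − b) × a_well].

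With a true 15% (control) and 12% (reminder), all assumed (differences from unrounded values):

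| Attendance well/ill, control; reminder | Deaths, control/reminder | Observed, control v reminder | Difference (true −3.0) |
|---|---|---|---|
| 90/90; 95/95 | 0/0% | 15.0% v 12.0% | −3.0 |
| 90/90; 95/95 | 2/2% | 13.3% v 10.2% | −3.1 |
| 90/90; 95/95 | 5/3% | 10.5% v 9.3% | −1.2 |
| 90/60; 95/85 | 0/0% | 10.5% v 10.9% | +0.3 |
| 90/60; 95/85 | 5/3% | 7.3% v 8.4% | +1.1 |

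Last row in full. Control: 0.10 × 0.60 / (0.10 × 0.60 + 0.85 × 0.90) = 0.060/0.825. Reminder: 0.09 × 0.85 / (0.09 × 0.85 + 0.88 × 0.95) = 0.0765/0.9125.

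Over a wider range (reminder-arm bad status 15%, 12% or 10%; deaths up to 8% v 5%; attendance as low as 85/40 in control and 95/80 in reminder), the shift against the reminder arm ran from essentially none to about 6 points.

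**4. What counting deaths achieves**
Add the deaths to numerator and denominator in the last row. Control: (0.05 + 0.060)/(0.05 + 0.825) = 12.6%. Reminder: (0.03 + 0.0765)/(0.03 + 0.9125) = 11.3%. The difference is −1.3 points: the right sign, but not the full −3.0, because ill survivors who were not seen are still missing.

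**5. Effect on the attendance outcome**
With deaths of 5% and 3%, if none of these patients had otherwise missed a visit, 5 − 3 = 2 points of the difference in Defaulters would be deaths.

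**The case against.** The strongest reply is that handling of deaths and missing visits belongs in the statistical analysis plan, which is not at hand, and that the protocol already names intention-to-treat beside complete case analysis. That holds for missing-data rules. It does not hold for the outcome components, the data items and the Defaulter wording, which are fixed here; no analysis plan can use vital status that was not collected.

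It is also fair that size and direction are assumed. Where illness does not affect attendance within an arm and deaths are equal, the bias is negligible. And the clinical part of H2 is not its only test: CD4 count and viral suppression form a separate secondary outcome.

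Three stronger readings are tempting, and the documents do not support them.
- A reader might infer that the reminder arm will look worse simply because it is seen more often. The main analysis is status at month 6, not a count of events over visits. What matters is mainly who attends that visit; extra visits bear on the every-visit records and the trend. An earlier TB episode can still show at month 6, since being on TB treatment is one of the groups.
- A reader might take the inputs of step 2 to show a reversal, 9.5% against 8.5% of all randomised patients. That requires unseen patients to be counted as event-free, a rule that the protocol does not contain. Among attenders those inputs give equality.
- A reader might want a cumulative yes/no composite of death, TB and opportunistic infection. TB and infections still need contact to be diagnosed, so it would carry the same dependence on attendance.

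**Conclusion.** The point holds in a limited form. Two parts rest on the text alone: clinical status is defined only from findings at attended visits, and death has no place in any outcome or data item, while the Defaulter wording takes it in without a rule for deaths.

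The bias is conditional. It needs ill patients to attend less, or more deaths in the control arm. Given that, a true benefit can be diluted to null (10% v 10% for a true 11% v 13%) or, with stronger assumptions, reversed (+1.1 instead of −3.0 points). If neither holds, there is no material bias. All rates are assumed. For scale, at 121 per arm and a proportion of 10% the standard error of a difference is √(2 × 0.10 × 0.90/121) = 3.9 points, so shifts of 0 to about 6 points range from negligible to larger than one standard error. The documents do not show that the bias will occur or which value it will take, but the change that guards against it is small and should be made.

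**What to change.** Amend Data collection, Primary Outcomes and Secondary Outcomes as follows.
- Add vital status at month 6 for every randomised participant, obtained in the same way in both arms from the hospital records and tracking contact already planned.
- Report deaths by arm.
- In the month-6 analysis, score death as the worst category of clinical status. Weight is continuous, so there death can be ranked last in a non-parametric test, or weight can be given for those seen with the number dead beside it.
- Code death separately from default and from loss to follow-up.
- Keep weight, TB status and WHO stage as month-6 measures. Report the number not assessed by arm, and add a sensitivity analysis for unseen patients, which step 4 shows is still needed once deaths are counted.

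The cost is protocol wording, a little more record abstraction, and use of tracking contact to establish vital status in both arms. Deaths outside the hospital may be missed where tracking fails; the protocol should say so.

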## RESEARCH APPROACH

### B. Research methodology

**Study Location:** The study will be conducted in Hospital Sungai Buloh, Selangor, Malaysia.

**Study Design:** It will be an experimental (randomized Controlled Trial) study design, single-blinded among newly diagnosed HIV positive patients who are eligible to commence ART from December 2013 to August 2014. Following enrollment and allocation to study arm, baseline adherence, clinical symptoms, CD4 count, viral load, Weight, TB status and Opportunistic infection index will be assessed and measured for the 2 groups, prior to the commencement of ART. The intervention group will receive appointment and medication reminders by text-messaging and telephone calls, in addition to standard care. Based on the Theory of Planned Behaviour Model (Ajzen, 1985), appointment reminders will be sent by Short Text Message (in Malay and English languages) three days prior to each individual client's scheduled appointment and telephone call reminders a day prior to the scheduled clinic appointment visits. Weekly short text messages will also be sent to clients to remind them of taking their medications. The control group will only receive standard care and paper-based appointment during clinic visits. Both groups of clients will be followed up for a period of 6 months on ART. Repeated CD4 count, viral load, Weight, TB status and OI index assessment and measurements will be conducted at 3 and 6 months, respectively to determine treatment outcome. Medication adherence will be measured using structured self-report questionnaires. Clinic visits will be measured through medical records of clinic attendance and clinicians' notes.

**Study Duration:** Recruitment and data collection will be from December 2013 to February 2015.

**Study population:** The study population is all HIV positive clients assessed and found to be eligible for ART commencement at Hospital Sungai Buloh, Selangor

**Inclusion criteria:** Age range of 15 to 65 years eligible to commence ART, able to read text messages and have a mobile phone access.

**Exclusion criteria:** Clients who are previously or currently on ART, foreigners & pregnant patients

**Sampling frame:** It is the list of all HIV positive clients assessed and found to be eligible for ART from December 2013 to August 2014 in Hospital Sungai Buloh, Selangor

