The other secondary outcome is (improved) immunologic status/response of patients at six months. This will be assessed based on records of two (2) laboratory measurements – CD4 T cell count and viral load. Patients' CD4 count results at six months will be assessed and compared with baseline values to determine if there's a consistent increase (or otherwise) as expected with strict medication adherence. If patients are adherent to ART regimens, absorb the drugs normally, and if their virus is not resistant to the ART drugs in the regimen, it is expected that their CD4 count should increase from baseline levels by at least 50 cells per microliter of blood within 6-12 months of initiating treatment. CD4 count value at six month scheduled follow-up is the primary analysis.

Similarly, plasma HIV RNA load results at six months will be assessed and compared with baseline levels to determine if there is a significant suppression at six months. If patients are adherent to ART regimens, absorb the drugs normally, and if their virus is not resistant to the ART drugs in the regimen, it is expected that their plasma HIV load should be suppressed to undetectable levels (<400 copies/ml) by six months and remain suppressed thereafter. Analysis of "suppressed" (<400 copies/ml) versus "failure to suppress" (>400 copies/ml) at six months as a dichotomous variable is the primary analysis.

**Data analysis:** Data collected will be collated, checked, cleaned, entered into and analyzed using Statistical Package for Social Sciences software (SPSS) version 21 and AMOS software. Parametric tests (T-test, repeated measures ANOVA) and non-parametric tests will be conducted on the data. P value for test of significance of results will be set at 0.05, alpha level (Type 1 error) at 0.05 (Confidence Interval of 95%), Power at 80% to detect an impact of 15% in the fraction of patients with adherence of at least 90% (assuming a no intervention median adherence level of 90%) using a two-tailed test, Z=1.96, and strength by effect size analysis. Analysis will be by intention-to-treat and complete case analysis.

| Independent variable                                                    | Dependent variable                                                           | Type of analysis                                                           |

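### The secondary outcomes are written as comparisons with the patients' own pre-ART baseline, and neither the outcome text nor the analysis table ties them to the intervention-versus-control contrast that H2 needs

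*Protocol*

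**What the plan says.** All places are in the protocol.

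- **Secondary Outcomes, clinical status.** Weight, TB status and opportunistic-infection status (by WHO stage) are assessed at each visit, "particularly at three and six months and comparing these with the baseline status".
- **Secondary Outcomes, CD4.** "CD4 count results at six months will be assessed and compared with baseline values", to see whether they have risen. The last sentence of that paragraph makes the month-6 CD4 value the primary analysis.
- **Secondary Outcomes, viral load.** Month-6 results are "compared with baseline levels to determine if there is a significant suppression at six months". The last sentence makes suppressed or not suppressed at month 6, with a cut at 400 copies/ml, the primary analysis.
- **Study Design.** Baseline measures "will be assessed and measured for the 2 groups, prior to the commencement of ART". Both arms are then followed for 6 months on ART. Patients with earlier ART are excluded.
- **Research hypotheses, H2.** Reminders improve adherence and clinical outcomes "when compared to routine adherence counselling and paper-based appointment scheduling alone". Expected outcome 2 also sets intervention against control.
- **Data analysis table.** For weight, CD4 and viral load as continuous outcomes, the independent variables are social and demographic characteristics, behaviour and adherence, and the methods are the t-test and repeated measures ANOVA. Study arm is not listed. The row for categorical outcomes (including TB status, OI index and viral suppression) refers to all independent variables without naming them.

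**The concern.** H2 is a question about two randomised arms. The Secondary Outcomes text describes a comparison within patients over time, and no arm appears in it. Between the two time points every patient goes from no ART to ART. The protocol itself expects ART, taken as directed, to raise CD4 by at least 50 cells and to suppress viral load within the follow-up period. Improvement from baseline is therefore expected in both arms whether or not reminders work.

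An analyst who followed these paragraphs and the table row literally would test a time effect and report an increase or a suppression. That result would say that ART works. Set beside H2, it could be mistaken for support for the reminders.

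**Working it through.** **1. Comparator stated for each outcome**

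| Outcome | Comparator in the outcome text | Arm named there? | Primary analysis named |
|---|---|---|---|
| Weight, TB, OI/WHO stage | baseline status | no | six-month follow-up |
| CD4 | baseline values | no | month-6 value |
| Viral load | baseline levels | no | suppressed or not at month 6 |

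The last column fixes a time point and a scale. It does not say what is compared with what. The table row for weight, CD4 and viral load does not supply the missing term, because study arm is not among its independent variables. A repeated measures ANOVA without an arm-by-time term would return the same time effect.

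**2. The sample-size inputs**

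The Sample size paragraph gives SD 132, two-sided alpha 0.05, 80% power and means of 550 and 500.

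n = 2 × 132² × (1.96 + 0.842)² / 50² = 109.4, so 110 per group.

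This reproduces the stated 110, with the difference squared; the printed expression divides by 50 and would give about 5,472. Adding 10% gives 121 per group. The 500 is defined as the baseline mean and the 550 as the mean after ART, so the difference of 50 is also a before-after difference. The point made here does not depend on that calculation.

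**3. What a within-arm before-after test would show if reminders had no effect**

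Inputs:
- mean rise 50 in each arm, a figure that the protocol gives for adherent patients and that is here applied to a whole arm;
- SD 132 at each time point;
- 121 × 0.90 = 108.9, so 109 completers per arm;
- correlation r between baseline and month 6, which the protocol does not give and which is therefore an assumption shown as a range.

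Formulas: SD of change = 132 × √(2(1 − r)); noncentrality = 50 / (SD of change / √109); probability of p < 0.05 from the noncentral t with 108 degrees of freedom.

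| r (assumed) | SD of change | Noncentrality | P(significant), one arm | P(significant), both arms |
|---|---|---|---|---|
| 0.3 | 156.2 | 3.34 | 91.2% | 0.912² = 83% |
| 0.5 | 132.0 | 3.95 | 97.5% | 0.975² = 95% |
| 0.8 | 83.5 | 6.25 | about 100% | about 100% |

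These figures are power to detect a real ART effect. In the same situation a between-arm test at month 6 has no true difference to find and would be significant at its nominal 5%.

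**The case against.** The strongest reply is that the protocol does point to the right contrast. It is a 1:1 randomised trial analysed by intention to treat. H2 and expected outcome 2 put intervention against control. The primary analyses named for CD4 and viral load are month-6 quantities, not changes. The two primary outcomes are also defined without naming an arm, so this may simply be the document's style, with the hypotheses supplying the contrast. No paired test is specified, and the t-test and repeated measures ANOVA can both carry a between-arm comparison. The reference to all independent variables in the categorical row may be meant to include study arm. The CD4 sentence also links the increase to strict adherence, which fits H3 and specific objective 4, where within-patient change is a legitimate measure.

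Most of this stands. A reader might infer that the secondary outcomes will be judged by a before-after test, or that the trial runs a type I error of 91% or more. The documents support neither: the primary analyses named are not before-after tests, and the percentages above belong to a test that the protocol does not prescribe.

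The reply does not remove the gap. For these outcomes a comparator is written, and it is the baseline. The viral-load sentence attaches the word significant to that comparison. The one table row that covers weight, CD4 and viral load lists its independent variables and leaves study arm out. The issue is therefore not detail left to an analysis plan, because the text in place points away from H2.

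**Conclusion.** The point holds as a fault in specification. The outcome text gives the pre-ART baseline as the only comparator for the secondary outcomes, the table row for weight, CD4 and viral load omits study arm, and the between-arm contrast of H2 is never attached to these outcomes. Comparison with baseline reflects the start of ART and cannot test H2.

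As to size, under the assumptions in step 3 a within-arm before-after test of CD4 would probably be significant in both arms with no reminder effect (about 91% to 100% per arm). The correlation is assumed, and the 50-cell rise is stated only for adherent patients, so a smaller average rise in a whole arm would lower these figures. They illustrate how little such a comparison says about reminders. The primary outcomes are not touched by this point.

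**What to change.** In the Secondary Outcomes text and the Data analysis table, name study arm as the independent variable and state that H2 is tested by intervention versus control at month 6:

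- **CD4 and weight:** between-arm difference in the month-6 value, adjusted for the baseline value.
- **Viral load:** between-arm difference in the proportion below 400 copies/ml.
- **TB status and WHO stage:** between-arm comparison of the month-6 categories.

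Add one sentence saying that change from baseline within an arm is descriptive with respect to H2. It can be kept for H3, where the question is how adherence relates to outcome.

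The cost is the wording of the outcome definitions and the table. The baseline and month-6 measurements are already planned, so no new data or visits are needed.

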Hence, sample size of 121 per group will be used for the study

**Intervention Protocol:** For the intervention group – a ‘reminder module’ will be developed and delivered via SMS and telephone calls by 2 PLHIV (research assistants). This will include weekly SMS medication reminders, SMS reminders 3 days prior to scheduled clinic appointments and telephone call reminders a day prior to scheduled clinic appointment (in addition to standard care – adherence counseling). To ensure confidentiality, typical medication reminder text messages will include a short slogan in Malay language “Apa khabar” “Ini untuk menberithau anda ubat” meaning “How are you?” “This is to remind you of your medications”. Appointment reminder text message would be “Apa khabar” “Tolong ingat tarikh temu janji lusa” meaning “How are you?” “Remember your appointment day after tomorrow” and telephone conversation would be standardized and short, with the message “Apa khabar” “Tolong ingat tarikh temu janji besok” meaning “How are you?” “Remember your appointment tomorrow”. The control group will receive standard care - routine adherence counseling only. Patients will not be required to provide any responses to the text messages. A call and SMS log will be recorded and kept. Two PLHIV that are stable and have been consistent and adherent to ARV medications for at least 2 years will be recruited as research assistants. Using standard training module developed and validated by a team of experts from Universiti Putra Malaysia and Hospital Sungai Buloh, a two-day onsite training of the research assistants on HIV prevention methods, care and treatment issues and how to respond to common questions related to medication adherence, including medication side effects, when asked by study participants, will be conducted. In addition to sending SMS and making telephone calls to patients, they will also be required to provide counseling support and provide guidance to patients (when required) in filling out medication adherence questionnaires during every clinic visits. Patients in the intervention group will be further divided into 2 sub-groups, each under the supervision of one research assistant, who will be responsible for providing them with counseling and psychosocial support, in addition to the care and management provided by the clinicians and nurses, throughout the duration of the study. Each patient in the intervention group would undergo a minimum of three (during clinic visits at month 1, month 3 and month 6) individual counselling sessions with the research assistants lasting an average of 15 minutes per encounter. An intervention manual containing the training modules and implementation guidelines will be provided to the research assistants as spiral-bound hard copy reference document, to guide their interactions with the patient and assure quality and uniformity in the implementation of the intervention.

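### The 80% power claimed for a 15% gain in the fraction with at least 90% adherence is not delivered by 121 per arm, a number set on CD4, and the 90% cut matches no declared primary analysis

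*Protocol*

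**What the plan says.** All references are to Protocol section B, Research methodology.

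- **Data analysis** gives a power statement for adherence: "Power at 80% to detect an impact of 15% in the fraction of patients with adherence of at least 90" per cent, with the condition "assuming a no intervention median adherence level of 90" per cent. The test is two-tailed with Z = 1.96 and alpha 0.05.
- **Sample size** uses a two-mean formula for CD4 count: SD 132 cells/µl, a difference of 50 (550 against 500), 80% power, and 1.96 and 0.842 as the normal quantiles. This gives 110 per group. Adding 10% for attrition gives 121: "Hence, sample size of 121 per group will be used for the study".
- **Secondary Outcomes** lists CD4 count under immunologic response.
- **Primary Outcomes** makes adherence at six months the first primary outcome. Good adherence requires an "optimal adherence cut of >95% of medications taken as directed", Fair is 80 to 95% and Poor is below 80%. On the form of analysis: "Percent adherence will be analyzed as continuous variable and polytomous variable".

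**The concern.** The adherence sentence is the only power statement the protocol makes for either primary outcome, yet no calculation connects it to 121 per arm. The only calculation shown concerns another variable, on another scale, that is not primary. Two questions follow: does 121 per arm deliver the stated 80%, and does the statement describe an analysis the trial will make?

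What is at stake is how a null adherence result is read. If the design has the stated 80%, the stated effect would be missed one time in five. If it has 62 to 66%, it would be missed between one time in three and two in five. A reader relying on the sentence would give a null result more weight than it deserves.

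**Working it through.** **1. The plan's own sample size.** With the squared difference in the denominator:

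n = 2 × 132² × (1.96 + 0.842)² / 50² = 2 × 17,424 × 7.851 / 2,500 = 109.4, so 110 per group.

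The protocol's figure reproduces. (The formula as it appears in the text, dividing by 50 rather than 50², would give about 5,472, so the squared form was evidently used.) Then 110 + 11 = 121. No adherence quantity enters.

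**2. Inputs for the adherence comparison.** From Data analysis: an effect of 15%, two-sided alpha 0.05 and a control median of 90%. From Sample size: 121 enrolled per arm, about 110 evaluable after the attrition allowance. The control proportion at or above 90% is not stated. A median of 90% puts at least half of controls there, and about half if few sit at exactly 90%. So p₁ = 0.50 (assumption) and, reading 15% as absolute points, p₂ = 0.65.

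**3. Sample size for 80% power**, with p̄ = 0.575:

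n = [1.96 √(2 p̄(1 − p̄)) + 0.842 √(p₁(1 − p₁) + p₂(1 − p₂))]² / (p₂ − p₁)²

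= [1.96 × 0.6991 + 0.842 × 0.6910]² / 0.0225 ≈ 169.3, so 170 evaluable per arm.

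**4. Power at the planned size.** Power = Φ{[0.15 √n − 1.96 × 0.6991] / 0.6910}.

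- n = 121: (1.650 − 1.370) / 0.691 = 0.405, power 65.7%.
- n = 110: (1.573 − 1.370) / 0.691 = 0.294, power 61.6%.

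Other two-sided methods at n = 121 agree: unpooled 66.6%, arcsine 65.9%, exact enumeration of the chi-square test 65.5%, continuity-corrected 60.3%. Even a one-sided 0.05 test, which the protocol does not plan, gives 76.5%.

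**5. Detectable gain.** From 50%, 80% power is reached at a gain of about 17.6 points with 121 per arm and about 18.5 points with 110.

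**6. Sensitivity to the unstated inputs** (same formula):

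| Control vs intervention | Power, n = 110 | Power, n = 121 | n per arm for 80% |
|---|---|---|---|
| 50% vs 57.5% (relative 15%) | 19.9% | 21.4% | 693 |
| 50% vs 65% | 61.6% | 65.7% | 170 |
| 60% vs 75% | 66.3% | 70.5% | 152 |
| 65% vs 80% | 70.5% | 74.6% | 138 |
| 70% vs 85% | 76.3% | 80.2% | 121 |

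A control rate of 70% is compatible with a median of 90% only through ties. At most 50% can lie strictly above the median, so at least 70 − 50 = 20% of controls would have to sit at exactly 90%.

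**7. The cut.** The powered variable splits patients at 90%. The declared categories split at 80% and 95%, so 90% falls inside Fair and the powered comparison cannot be recovered from Good, Fair and Poor. Nor is it the continuous analysis.

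**The case against.** **The control rate is inferred.** The protocol never states 50%. Adherence is computed from missed doses over 30 days, which is a coarse scale: with one dose a day, three missed doses is exactly 90%. Ties are therefore plausible and would raise the control rate. This stands, and it is why the 62 to 66% must be given as conditional. It does not rescue the claim: 80% needs at least a fifth of controls at exactly 90%, which the protocol nowhere assumes, and all 121 per arm evaluable. With 110 evaluable, the power is still 76%.

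**The primary analysis may have better power than this.** The continuous form of percent adherence is also declared, and its power has not been assessed here. That is right. The finding is that the stated figure is wrong for the comparison it names, not that every adherence analysis is weak.

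**A reader might infer an inflated type I error.** There are two primary outcomes; the second is treated in the same way as the first ("Number of missed appointments will be analyzed as a continuous variable and polytomous variable"), and one level is given, "alpha level (Type 1 error) at 0.05 (Confidence Interval of 95" per cent. From this one could count four tests at 0.05. The documents do not support that step. They do not say that each form, or each outcome, is a separate route to claiming success. If both outcomes had to succeed, no split would be needed. Two forms of one variable are not independent tests. A multiplicity rule and the choice of decisive form may also sit in a statistical analysis plan that is not shown.

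**Conclusion.** The power statement is wrong as written. On the natural reading (absolute 15 points, about half of controls at or above 90%), 121 per arm gives about 66% power and about 62% with 110 evaluable, against the stated 80%; 170 evaluable per arm would be needed. With ties raising the control rate to between 60% and 70%, the range is 66 to 80%, touching 80% only at the extreme of that range and with no attrition. A relative 15% gives 20 to 21%. The discrepancy arises because the sample size was set on CD4, a secondary outcome.

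Separately, and without any assumption, the 90% cut matches no declared primary analysis.

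The 66% should not be quoted unconditionally, because it rests on the assumed 50% control rate. Nor does the finding show that enrolment must rise: the CD4 calculation supports 110 per arm for its own stated difference.

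**What to change.** Change the wording in Data analysis and Sample size; enrolment stays at 121 per arm.

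1. Replace the 80% claim with what the design gives. For example: with 121 enrolled (about 110 evaluable) per arm, and assuming 50% of controls reach the cut, a rise of 15 absolute points has about 62 to 66% power, and about 17.6 to 18.5 points is detectable with 80% power.
2. Express this for the declared >95% Good cut, over a stated range of assumed control rates, since the protocol gives none. If the 90% control median is kept, at most half of controls can exceed 95%. As an illustration for a 15-point gain, 40% vs 55% has 61 to 65% power. The formula is unchanged when both proportions are replaced by their complements, so 30% vs 45% equals 55% vs 70% (63 to 68%), and 20% vs 35% equals 65% vs 80% (71 to 75%).
3. State that the sample size was set on CD4, a secondary outcome, and that the adherence figures describe the resulting design.

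The cost is a less favourable stated power. Rewording does not raise the power itself, but readers can then judge a null adherence result correctly.
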